### Aim 2 effect of ZAIMARA on AGYW HIV testing uptake at 6-months

**Overview**. AGYW and MF will be recruited from five geographically distinct communities and randomly assigned to the experimental (ZAIMARA) or control (health promotion) arm as a dyad. They will complete surveys at baseline, 6-, 12-, 18-, and 24-month follow-up using computerized assisted self-interview technology (CASI). AGYW will provide urine for STI screening, and we will offer HIV testing and pre-exposure prophylaxis (PrEP) at each time point. AGYW will receive healthcare free of charge at the site clinic as needed, including STI treatment in line with national guidelines. ZAIMARA and HP workshops will be delivered over 2-days (~ 12 h) and matched in time and intensity. Day 1 will last approximately 6-hours and include eligibility screening, consent/assent, the baseline survey, randomization, workshop day 1, and clinical assessments (HIV and STI testing, PrEP uptake). AGYW and MF will return to the site on a separate occasion (approx. 1 week later) for workshop day 2 of the intervention (~ 8 h). Sessions are conducted with AGYW and MF together and separately. To enhance the workshop experience and ensure participants’ comfort, light snacks, lunch and beverages will be provided during both workshops.

**Study sites**. The study will be conducted in five geographically distinct catchment areas in Lusaka, each feeding into a Ministry of Health (MoH) district clinic or hospital. The sites were chosen based on the high volume of adolescents seeking SRH services and the surrounding community population of AGYW. We expect enrollment of at least 2–3 AGYW-MF dyads per day per site.

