**Recruitment.** Research staff, with assistance from neighborhood health committee (NHC) members will recruit AGYW and MF. NHC members are well-known in the community and recognized by the MOH as responsible for mobilizing and sensitizing communities about cross-cutting health issues, including research studies. The project coordinator will train NHC members to deliver recruitment messages using the recruitment brochures, and they will accompany outreach sessions. Recruiters will establish a landmark location in the neighborhood from which they can easily approach (or be approached by) women and AGYW. NHC members will initiate contact with a potential participant (AGYW or MF) and ask if she would like more information about the project. If yes, the research staff will explain the study and screen for inclusion/exclusion criteria. In addition, NHC members and research staff will implement a systematic door-to-door sensitization and recruitment strategy. Specifically, they will visit every fourth household within each selected neighborhood. During these visits, they will provide information about the study, address any questions or concerns from potential participants, and conduct preliminary screening to assess eligibility for study enrollment.

We will enroll approximately 16–20 dyads twice per month at each site for one year, beginning with two sites and then adding the remaining three sites. NHC members will receive approximately 50 kwacha (approx. 2 USD) for each eligible AGYW referred to the study to cover associated text/call costs and 50 kwacha to cover transport costs.

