**Participants**. We will enroll up to 650 AGYW-MF dyads (120–130 dyads per site) for a total of 1200 to 1300 individuals. AGYW will be 15–19 years-old, female sex assigned at birth, unmarried, reside within the study catchment area, speak IciNyanja, ChiBemba, or English or a combination (the primary regional languages), willing and able to provide consent (≥ 18 years old) and/or assent (< 18 years old), and not known to have HIV (i.e., no positive test and not on ART). AGYW who participated in study Phase 1 or are enrolled in another sexual health intervention at the research site will be excluded. AGYW may or may not be sexually active; information about AGYW sexual activity will not be shared with MF. AGYW who test positive for HIV at baseline will complete the workshop, but then they will exit the study because it is not designed to provide support for persons with HIV. AGYW who become pregnant during the study may continue to participate.

MF are defined as an important and influential female in AGYW’s life (e.g., mother, aunt). MF will be chosen by the AGYW and agreed upon by the guardian/mother. MF must be ≥ 24-years-old, living with or in daily contact with the AGYW, speak IciNyanja, ChiBemba, or English or a combination, and willing and able to provide consent. MF who participated in study Phase 1 will be excluded.

**Consent/assent**. Study staff will explain research activities separately to MF and AGYW, allowing for independent consent and assent to prevent coercion. AGYW and MF must agree to participate as a dyad, but AGYW refusal will supersede MF consent. Consent/assent forms will explicitly state exceptions to confidentiality, for example, findings of suicidal ideation requiring referral, and these will be verbally reviewed with participants. The consent and assent documents will state that no information about AGYW sexual activity or HIV and STI test results will be shared with MF, reducing this barrier to consent/assent.

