**Randomization**. We will randomize AGYW-MF dyads to one of two conditions (ZAIMARA or HP) following the baseline assessment (Fig. 1). We will use stratified permuted block randomization (blocks of 2) to ensure uniform distribution across arms and a balanced allocation (*n* = 300–325 ZAIMARA and *n* = 300–325 HP) throughout enrolment. AGYW and MF dyads will be randomized to the same condition. By stratifying the randomization process at the clinic level, we will account for potential variations in participant characteristics by neighborhood or clinic-specific factors, enhancing the validity and reliability of the study findings. Pre-determined randomization logs at each site will guide assignment to arms.

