This study has additional strengths. We will collect both quantitative and qualitative data to allow for a deeper examination of participant and partner experiences and to strengthen ZAIMARA adoption, acceptability, appropriateness, and feasibility. The study draws on the unique expertise and partnership between U.S. and Zambian investigators ensuring that the intervention and the study design reflect genuine contributions by both sides. Indeed, prior to submitting any funding application, the intervention and study design were extensively vetted with key Ministry of Health staff, the MOH Adolescent Technical Working Group, and the CIDRZ adult and adolescent community advisory boards for concurrence. By engaging MF and AGYW together, ZAIMARA amplifies the impact of their relationship on SRH, because they can support one another in efforts to adopt prevention behavior. Lastly, ZAIMARA offers a combined behavioral and biomedical intervention package on-site, eliminating typical barriers to accessing HIV testing, PrEP, and STI testing and treatment.

Limitations of the study exist. We will rely on self-reports of MF-AGYW communication and relationships, and self-report data may suffer from recall and social desirability biases. To combat this risk, we will use a standardized self-administered CASI assessment system at all time points, with research assistants blinded to arm, and not peer leaders, helping AGYW and MF complete the survey. We will employ resident NHCs to recruit participants, and they may deliberately choose specific AGYW and MF in favor of their personal networks or possibly target AGYW who they deem are at ‘high risk’, hereby biasing our sample. To address the potential for selection bias, we will pair a research staff with NHC recruiters to ensure compliance with rigorous recruitment procedures. To minimize bias in assignment to condition, we will randomize MF-AGYW dyads and peer leaders to arm and evaluate any baseline differences that might influence effectiveness outcomes. Scalability and sustainability will be measured prospectively. Changes in leadership, country priorities and funding may affect the subsequent rollout and sustainability of the program. Finally, this trial will occur across five distinct geographical areas, and findings may not generalize to other districts/provinces.

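### Permuted blocks of 2 within clinic make the second allocation of every pair certain to anyone who knows the block size and sees the first

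*Protocol article*

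**What the plan says.** The Randomization paragraph under Aim 2 gives one block size for dyads: "We will use stratified permuted block randomization (blocks of 2) to ensure uniform distribution across arms". Each clinic has its own sequence ("By stratifying the randomization process at the clinic level"), and the paragraph adds: "Pre-determined randomization logs at each site will guide assignment to arms". Assignment takes place "following the baseline assessment".

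The Aim 2 overview puts these steps on day 1 in this order: "eligibility screening, consent/assent, the baseline survey, randomization, workshop day 1". On numbers, the Recruitment paragraph says "We will enroll approximately 16–20 dyads twice per month at each site for one year", and the Participants paragraph gives 120–130 dyads per site, up to 650 in total. The Contamination paragraph places the two programmes in different spaces at the site. The only dyad-level blinding described is in the Discussion and covers the research assistants who help with the surveys.

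**The concern.** In a block of 2 the second place is whatever the first was not. The first assignment does not stay hidden for long: randomisation and the first workshop fall on the same day, and the arms go to different rooms. Anyone who assigns dyads or directs them to a room can follow the sequence. The block size is published, and could in any case be inferred after watching a few pairs.

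The primary outcome is uptake of HIV testing, a voluntary behaviour that may well depend on motivation and family support. If a better-motivated dyad could be placed in a slot known to be ZAIMARA, the arms would differ for a reason unrelated to the programme. The Statistical analysis section adjusts for potential confounders found unbalanced at baseline. That would not reliably correct for motivation that no baseline item captures.

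**Working it through.** **The plan's own sample-size figure.** 300 per arm less 10% attrition is 300 × 0.90 = 270. For 0.454 versus 0.574, the unpooled standard error is √[(0.454×0.546 + 0.574×0.426)/270] = 0.0427. Power is Φ(0.12/0.0427 − 1.96) = 80.2%, and the risk ratio is 0.574/0.454 = 1.26. The figure reproduces and does not depend on the block size.

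**Predictability of blocks of 2.** The inputs are block size 2, five clinics, 120–130 dyads per clinic and 600–650 in total, all from the Aim 2 section.
- Certain allocations: one of every two. This is 60–65 per clinic and 300–325 overall (50%).
- Correct guesses: the first of a pair is right with probability 0.5 and the second with probability 1, so (0.5 + 1)/2 = 75%.

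**Alternatives.** In a fixed block of 2b, the expected share of certain allocations is 1/(b+1). Correct guesses come from enumerating every possible block and always guessing the arm with more places left. For mixed sizes the figures come from simulating 1,000 sequences of 130 dyads, with an observer who knows the set of sizes but not the current one.

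| Scheme | Certain | Guessed correctly |
|---|---|---|
| Fixed 2 (plan) | 50% | 75% |
| Fixed 4 | 33.3% | 70.8% |
| Fixed 6 | 25% | 68.3% |
| Mixed 4/6, undisclosed | about 5.5% | about 69% |
| Mixed 4/6/8, undisclosed | about 2.3% | about 68% |

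If a whole session is randomised at once, nothing has been revealed when dyads are ordered or deferred, so neither action gives information about the arm.

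**What steering could do (illustration, assumed inputs).** Suppose there is no true effect, both rates are 0.454 and there are 270 per arm. Half the places are predictable. Let f be the share of those that is steered, and g the difference in testing probability between dyads steered to the two arms. The spurious difference is 0.5 × f × g. The null standard error is √(2×0.454×0.546/270) = 0.0429.

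| f | g | Spurious difference | Two-sided type I error |
|---|---|---|---|
| 0.10 | 0.10 | 0.005 | 5.2% |
| 0.25 | 0.20 | 0.025 | 9.0% |
| 0.50 | 0.20 | 0.050 | 21.5% |

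The design difference is 0.12. The documents give neither f nor g.

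**Session balance.** Splitting 16–20 dyads equally gives 8–10 per arm, within the ideal group size of 6–10 in the intervention description. With mixed 4/6/8 blocks the running imbalance can reach 4 either way. A session that starts 4 behind in ZAIMARA and ends 4 ahead has gained 8, so 16 dyads could split 12/4.

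**The case against.** The other side has several good arguments.

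- Three stronger readings are tempting. The first is that the site logs are open to view. The article does not say who holds them or whether entries are sealed, and an article may leave that to the full protocol. Concealment is therefore not part of this point. Sealing the log would not cure the problem, though, because the second allocation follows from the first as soon as the first is seen.
- The second is that the trial is simply unblinded. The article does not use the term, and its survey assistants are blinded to arm. Participants, peer leaders and whoever makes the assignment still know the arm.
- The third is that the article admits to selective assignment when it says of recruiters that "they may deliberately choose specific AGYW and MF in favor of their personal networks". That sentence concerns who enters the sample. Recruiters are given no role in allocation.
- Randomisation follows consent and baseline, so refusing eligibility in view of a known arm is largely closed off. The article does not say who orders the dyads, or whether they are assigned singly or together. This stands, and it narrows the route to entry order or deferral.
- Blocks of 2 serve a purpose: they keep the parallel groups equal. Larger varying blocks give up some of that balance and lower correct guesses only from 75% to about 68%. This also stands, and it decides the choice of remedy.

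**Conclusion.** The point holds in this limited form. A fixed block of 2 within clinic makes 50% of allocations (300–325 of 600–650) certain, and 75% are guessed correctly, by an observer who knows the block size and sees each assignment. The rule is stated in the article, so this is not a matter of missing detail.

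That allocation will be steered is not shown. The effect on the result depends on assumed values and runs from negligible (type I error about 5%) to material (about 21%) in the illustration. The weakness lies in the primary comparison, analysis could not reliably repair it afterwards, and removing it costs little.

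**What to change.** Replace blocks of 2 with randomisation of each session's dyads as one 1:1 batch within site, after all that session's baseline surveys are complete. Release the assignments centrally, for example through REDCap, which the study already uses, or through someone not involved in recruitment. For an odd-sized batch, draw at random which arm takes the extra dyad. With 16–20 dyads per session this keeps 8–10 per arm and needs no extra sample size or staff. The cost is in timing: nobody can be assigned until the last 1.5-hour survey is finished, on a day of about 6 hours that also holds the first workshop.

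Second best are larger, randomly varying blocks that are not disclosed to sites. Mixed 4/6/8 cuts certain allocations to about 2%, but leaves correct guesses at about 68% and can unbalance a single session, up to 12/4 of 16.

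If enrolment has begun, apply the change to the remaining dyads and document the switch date.

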**Fig. 1 Fig1:**
[figure not shown]
Flowchart for ZAIMARA intervention versus Health Promotion for AGYW-MF dyads

**Peer leaders**. Peer leaders (*N* = 60) will be female and live in the community where the program is delivered, have prior experience working with young people, have a minimum grade 12 education, and be proficient in reading and writing English and/or IciNyanja or ChiBemba. ZAIMARA and HP will be co-facilitated by four female peer leaders, each as follows: two peer leaders, ages 22–29 years-old will co-facilitate ZAIMARA to AGYW, and two peer leaders ages 30 years and older will co-facilitate ZAIMARA to MF. Likewise, two peer leaders ages 22–29 will co-facilitate HP to AGYW, and two peer leaders ages 30 years and older will co-facilitate HP to MF. Randomization will be stratified by clinic site, intervention arm, and age (22–29 years-old or ≥ 30 years-old).

**Training peer leaders.** Training for both interventions will stress the importance of following a standardized manual to ensure treatment fidelity across peer leaders. We will discuss group dynamics that may arise during the sessions and strategies to address them. Peer leaders will receive their curriculum in advance of the training to read and prepare questions for the in-person training. Training will occur over two weeks or approximately 30 h, led by two local ZAIMARA trainers who were trained by experienced IMARA SA facilitators during Phase I. During training week one, peer leaders will observe and act as group participants as the trainers demonstrate each activity in the curriculum. During week 2, the peer leaders will practice delivering the curriculum to each other. Two peer leaders will co-facilitate an activity while the remaining peer leaders observe and act as group participants. Peer leaders will rotate who delivers the intervention and who observes throughout the week so that all peer leaders have an opportunity to facilitate and observe. As peer leaders practice facilitating the interventions, the trainer and other peer leaders will provide feedback to improve delivery and strengthen treatment fidelity. The peer leaders will continue to practice until they are “certified” as competent (e.g., adherent, comfortable) to deliver ZAIMARA or HP by the trainers and investigators. We will conduct re-trainings as needed to prevent implementation drift. We will train new peer leaders using the strategies described above. They will observe one full intervention cycle by experienced peer leaders and participate in supervision prior to delivering the program.

**Supervision and quality assurance**. We will use a manualized curriculum and facilitator guide, weekly supervision, and observer ratings of adherence and competence to ensure treatment fidelity. Three locally trained nurses will provide weekly supervision to peer leaders separated by treatment arm. Two nurses will be trained to supervise ZAIMARA, and one nurse will be trained to supervise HP. Weekly supervision will include all trained peer leaders in the same treatment arm at the same site, even if they do not deliver the program (e.g., observers). Supervisors will review treatment fidelity forms in advance of supervisory sessions to identify potential challenges and areas lacking fidelity. They will refer to fidelity forms during supervision as needed. Supervisors and peer leaders will discuss session activities and problem-solve challenges. Weekly supervision will enhance quality assurance and quickly identify if a peer leader(s) deviates from the curriculum. In this case, the peer leader(s) will be re-trained until fidelity is achieved.

**Treatment fidelity.** All workshop sessions for both treatment arms will be observed by a trained peer leader who will be present during the intervention to assess treatment fidelity. Local ZAIMARA/HP trainers will observe 25% of the sessions. All observers will rate peer leaders on adherence and competence at the end of each workshop day. We will determine fidelity to ZAIMARA and HP by calculating the percentage of activities delivered (i.e., adherence) and peer leader mean competence rating.

## Intervention descriptions

**ZA****mbian**
**I****nformed**
**M****otivated**
**A****ware and**
**R****esponsible**
**A****dolescents and Adults (ZAIMARA)**. IMARA (see Table 1) was derived from three CDC-designated evidence-based interventions: SISTA (Sisters Informing Sisters about Topics on AIDS) [44], SiHLE (Sistering, Informing, Healing, Living, and Empowering) [45], and Project STYLE (Strengthening the Youth Life Experience) [46]. IMARA engages AGYW and their MF to address the individual, sociocultural, and structural factors that influence AGYW’s sexual behavior [32]. Ideally ZAIMARA is delivered in groups of 6 to 10 participants, with certain activities conducted separately for MF and AGYW, while others are implemented jointly. The separate MF and AGYW groups run simultaneously, covering parallel content. Joint activities are designed to enhance MF’s credibility as a resource for HIV/STI prevention and facilitate the practice of new skills. Additional activities focus on conflict negotiation, assertive communication, and strengthening the AGYW-MF relationship. The material is presented in a group format to promote structural change, build community norms for prevention, and reduce HIV stigma.

Beginning with an icebreaker and/or a national poem to enhance Zambian and gender pride, facilitators then review ZAIMARA’s goals. The program motto is presented to emphasize strong AGYW-MF relationships, foster sisterhood and community empowerment, build group cohesion, and increase motivation for HIV/STI prevention [47]. At the start of the workshop on day 1, each MF and AGYW signs the ZAIMARA pact to confirm their commitment to the program. ZAIMARA spans approximately 10–12 h, delivered over two days, ideally separated by one week to allow participants time to assimilate information. At the end of workshop day 1, MF and AGYW are given homework to complete before workshop day 2. ZAIMARA weaves in the impact of mental health issues and alcohol and drug use on HIV/STI risk (e.g., condom use while inebriated) throughout the curriculum.

**Table 1 Tab1:** Overview of ZAIMARA

Theory	Selected IMARA activities
***Individual factors***	
Knowledge about HIV, STI, PrEP, HIV testing and attitudes about PrEP	Facts of HIV/AIDS/STI/PrEP/HIV Testing; Prevalence and incidence for women; Perceived vulnerability; Personal risk triggers (people, places, feelings) and risk plans; Demonstrate and practice condom use; Importance of regular HIV testing and PrEP use where appropriate to risk behavior
Mental health	Destigmatize mental health; Links between mental health problems and HIV risk behavior; Recognize how feelings trigger risk-taking; Teach healthy coping strategies; Referrals for counseling
***Social factors***	
Family context	Importance of strong AGYW-MF relationships, and open and positive communication; Review need for MF monitoring; Create personalized monitoring plans; Understand the impact of mental health on HIV/STI-risk; Increase AGYW-MF warmth and positive interactions; Teach and practice effective communication with partners and family
Geographically constrained networks	Discuss HIV/STI risk in the context of neighborhood and sexual networks
***Structural factors***	
Gender dynamics	Expectations of women; Media images; Healthy and unhealthy relationships; Gender Based Violence; Gender role expectations and stereotypes; impact of gender of dynamics on HIV/STI risk
Partner relationships	Implications of age discrepant partners and concurrent partnerships; Importance of HIV testing, STI testing and treatment, and PrEP use and persistence; Communication with partners about HIV testing and PrEP
HIV stigma and discrimination	Changes in community norms to reduce stigma toward HIV/STIs, PrEP, and HIV testing

**Health promotion (HP): Time- and attention-matched control**. HP will be delivered as the comparison program and was used as the control group in IMARA SA. HP focuses on promoting healthy living by encouraging good nutrition, regular exercise, and informed consumer behavior. Although the HP curriculum does not explicitly address HIV/STI prevention, it includes basic information about HIV and other STIs due to the high-risk for AGYW. Like ZAIMARA, HP uses interactive games, videos, worksheets, and group discussion and MF and AGYW will meet in separate groups and together.

**Contamination**. Contamination across arms will be minimized as follows. (1) Peer leaders will not overlap, and training will occur separately. (2) ZAIMARA and HP will occupy different spaces at the site to reduce participant contact.

**Retention.** At baseline, we will obtain AGYW and MF phone numbers, home address (and draw a map), and other contact information (phone/text/WhatsApp). We will collect the phone numbers, home addresses, and text/WhatsApp information for at least two persons who will always know how to reach them in the future. We will make reminder calls the day before each workshop day and follow-up assessments to confirm attendance, and we will update our locator information at each contact. If the phone number/text/WhatsApp is disconnected, we will contact people from participants’ records. If AGYW were recruited through a clinic site (vs. outreach), we will seek assistance from the health facility and NHC members to locate them. Research assistants will visit the AGYW’s and MF’s last known address to try to locate them in-person. If the AGYW and/or MF no longer live at the address, we will ask their contacts to help us locate them. We will continue to try to locate them until the window for their assessment closes.

**Study assessments.** AGYW and MF will complete 1.5-hour surveys via CASI at baseline, 6-, 12-, 18-, and 24-months post-intervention, and research staff will be present to answer questions and assist participants as needed. AGYW will provide a urine sample to test for three STIs (gonorrhea, chlamydia, and trichomoniasis). At the end of workshop day 1, AGYW will be offered HIV testing and PrEP (where appropriate). AGYW who want and are eligible for PrEP will receive a one-month supply or referral for PrEP depending on their preference and available supplies. They will also be referred to PrEP services closest to them for refills. AGYW may refuse HIV and STI testing and/or PrEP and remain in the study. AGYW and MF will each receive K200 (~$9.00) on both workshop days and each follow-up assessment, K200 for transport, and other incentives (e.g., T- shirts, sanitary towels, hygiene products such as soap at each visit) during in-person visits.

